#### Procedures on Day of clinic visit

Research assistants (RAs) approached women in the waiting room of FP clinics after they checked in for their clinic visit if they were not in the presence of a male partner and asked if they were here for a clinic visit today, and whether they would like to hear about a women’s health research study. If they were interested, the RA assessed for eligibility. If eligible, potential participants were brought to a private space in the clinic to complete the consent process and survey administration. RAs let clinic staff know that the patient may be interested in being in the study and would be taking the survey before her appointment if she consented.

RAs explained to potential participants that they would complete two surveys (one before and one immediately after their clinic visit today) and receive a $15 gift card, one survey in approximately 3 months for $25, and one survey in 12 months for $40 to thank them for their time and effort.

#### Prior to clinical encounter

Before participants’ appointments, they provided their contact information (phone number and email address) and two alternate contacts to the RA. RAs also went over the verbal consent sheet, which provided details on why the study was being conducted, the data collection process at each of the three time points, the implications of the Certificate of Confidentiality that was obtained for the study, the voluntary nature of participating, and the schedule of compensation. RAs then answered any questions participants had and asked participants to sign an optional medical chart release form (provided by the clinic) for chart abstraction at the conclusion of the study. After being assigned a four-digit ID number for the survey data, participants completed an audio computer-assisted survey instrument (ACASI) on a laptop with the option to have questions read aloud (in English or Spanish) through headphones. When participants finished with the baseline survey, they either returned to the waiting room to wait to be seen by the clinician(s) or went directly to an exam room for their scheduled clinical visit. RAs communicated with clinic staff to indicate which participants had taken the baseline survey so that they could direct the patients (after their clinical visits) back to the RAs for the exit survey.

#### Following clinical encounter

After the participants’ clinic visits, they were asked to return to the private room with the RA to complete the client exit survey, also completed using the ACASI program on a laptop. Upon finishing this survey, RAs issued $15 gift cards, local resource sheets, and appointment reminder cards for the next follow survey to all participants. In intervention clinics, RAs also offered extra palm-sized brochures to participants, explaining one was to keep, and one was to give away to either a friend or family member. Control clinic participants only received the one page community resource sheet. When distributing brochures and resource sheets to participants, RAs told participants that taking these materials was voluntary, if they felt safe taking the materials with them.

### Procedures for post-visit assessments

After T1 is complete, RAs communicate with participants via phone calls, texts, and emails to schedule the next two surveys at the clinic, online, or by phone. If participants gave RAs permission to leave voicemail messages, RAs leave messages explaining that “It’s time to complete the next step of the Women’s Health Study, please call ###-###-#### to make arrangements.” The RAs’ email addresses used for correspondence to schedule surveys and send online survey links lack features that identified the true purpose of the study (for example: [contact]). Language used in the email titles and bodies is also general and pertains to the “Women’s Health Study.”

Participants become eligible to complete their follow up surveys at three months (T2) post baseline and again at 12 months (T3) post baseline (Fig. 4). RAs schedule times to meet participants back at the clinic to complete the ACASI surveys. If participants 18 years and older are unable to come to the clinic they are offered the option of completing the survey online via Survey Monkey or over the phone. If a participant cannot come to the clinic and is under 18 year old, they are offered to the option to complete the follow up surveys via phone.

**Fig. 4 Fig4:**
[figure not shown]
Interview schedule. For patients not completing T2, a Non-respondent interview is collected to enhance retention at T3

If RAs are not able to contact a participant to schedule the T2 schedule within the three to 6 month window following baseline but regained contact thereafter, RAs offer the option of completing an interview about their experience with the study for $40 compensation. These interviews assess the barriers participants experienced such that they couldn’t complete T2 within the specified time frame. The most common barriers were not having time and not having access to a private computer to take the survey online. At the conclusion of this non-respondent interview (NRI), the interviewer worked with the participant to schedule her T3 survey.

The sub-sample of intervention participants over age 18 who complete T3 either in-person or by phone are asked whether they would be interested in learning about an optional study component. Interested participants complete a brief computerized screen to determine their eligibility for a narrative interview about their experiences receiving the intervention. The narrative interviews are intended for women who have ever experienced IPV or RC, as the intervention is likely to be most relevant for this subsample of women. Eligible women respond affirmatively on this screening survey to having ever experienced IPV or RC. The RA explains the interview would include sharing her relationship history as well as perspectives on receiving the intervention in the clinic. These interviews are conducted at the clinic at a time convenient for the woman, and she receives $50 to thank her for her time. Survey data are not connected to these anonymous narrative interviews.

At the conclusion of both T2 and T3 surveys, the same protocol for distributing gift cards, resource sheets, and safety cards is followed. If surveys are completed online or by phone, gift cards are mailed to participants with a generic return address that would not identify their participation in this study.

At the conclusion of T3 data collection, available FP medical records are reviewed for participants who had signed authorizations allowing the study team to do so (98 % of participants). RAs review visits spanning 12 months pre-baseline to 18 months post-baseline to record number and types of clinic visits, reasons for visits, pregnancy and STI testing and diagnoses, documentation of assessment for IPV and RC, and documentation of any disclosures of IPV or RC.

### Retention

Throughout the course of the study, research personnel use multiple methods to keep participants engaged in the study. One method is to call approximately 1–2 times per month to verify contact information. In addition participants are contacted to set up follow up surveys approximately 4–6 weeks before their “due” date, and then are reminded the day before and on the day of appointments. If a participant misses their window for participation in the T2 survey (beyond six months after baseline), they are contacted for a non-respondent interview (described above) where they are asked questions such as “We'd like to know what some of the reasons were that you were not able to do the survey?” and “What would have made it easier to come back to do the survey?” This information informs improvements to the protocol to add additional funds for bus fare on women’s gift cards, as transportation (and not having enough funds for gas) was a common reason stated for not being to make it to appointments.

### Power calculations and sample size

The planned recruitment of 3600 subjects from 25 clinics in 17 clusters was designed to achieve 80 % power to detect clinically significant effects of the intervention (under two-sided testing at alpha = 0.05) for each of the specific hypotheses, after making appropriately cautious adjustments for loss to follow-up, variance inflation arising from cluster randomization, repeated follow-up measurements (of most outcomes), the small number of denominator degrees of freedom available when 17 clusters are used to assess the effect of the intervention, and for the restriction of the Aim 2 analyses to subjects who reported recent IPV or RC victimization at baseline. Reduction of RC and IPV by 50 % (*OR* = 0.50) in both the full sample and subset experiencing IPV/RC at baseline were specified as clinically significant effects. We also specified that reduction in recent unintended pregnancy at the 12-month follow-up by 43 % (*OR* = 0.57) in the full sample would represent a meaningful clinical effect. Clinically significant effects were also specified for other primary and secondary outcomes, corresponding to intervention effect sizes of 0.20 standard deviations and 0.35 standard deviations for Aim 1 and Aim 2 analyses, respectively.

Calculations were guided by results from our pilot study, [26] allowing us to anticipate that the prevalence of recent reproductive coercion in the control group would be 10 % in the Aim 1 sample and 26 % in the Aim 2 sample and we powered the study to detect reduced prevalence of this outcome in the intervention arm of 5.3 % and 14.9 % in the Aim 1 and Aim 2 analyses, respectively. Similarly, assuming the prevalence of recent unintended pregnancy is 20 % in the control arm at the 12-month follow-up (from pilot data), our study was powered to detect a prevalence reduced to 12.5 % in the intervention arm in the Aim 1 analysis.

Based on results from the pilot study, we anticipated retaining at least 80 % of baseline subjects for the first follow-up assessment. We further assumed that at least 75 % of the subjects from the first follow up would also complete the second follow-up assessment, that approximately 17 % of subjects would report recent IPV victimization at baseline. To account for cluster randomization design effects, we assumed that in our planned regression analysis the residual within-person and within-clinic correlations would be no higher than 25 % and 1 % respectively for key outcomes. The above conditions indicate that our planned sample size of 3600 patients and repeated measurements for most outcomes would result in analyses that would provide an effective sample size for Aim 1 analyses of at least 798 for assessing the unintended pregnancy outcome (at the 12-month follow-up) and at least 1000 for the other Aim 1 outcomes (where observations at both follow-up occasions would be analyzed jointly – i.e., pooled T2 and T3 data). For the Aim 2, we anticipated an effective sample size of at least 424 observations for the other key outcomes in Aim 2 (where assessments from both follow-up occasions would be analyzed jointly). If attained, these effective sample sizes, based on prudently cautious assumptions, ensure at least 80 % power to detect clinically significant effects for the main outcomes in the analyses for Aims 1 and 2.

### Data safety and monitoring plan

The ARCHES intervention is focused on providing education, relevant counseling and support for females ages 16 to 29 years seeking care in family planning clinics. The pilot study enrolled over 1200 women, allowing for careful process evaluation to examine the impact of the intervention on client and clinic provider safety. To our collaborative team’s knowledge, no adverse events emerged in the course of the pilot implementation. We ensured that the intervention clinics received specific training on mandated reporting requirements and how to conduct this reporting in as safe and client-centered way as possible as an integral part of the intervention. In addition to usual precautions regarding protecting client privacy and confidentiality, we also obtained a Certificate of Confidentiality to protect the research data from subpoena. No requests for data occurred during the pilot study. Despite the low risk associated with this behavioral intervention, we organized an internal data safety and monitoring plan as well as an external data safety and monitoring board. The Internal Data Safety and Monitoring board is comprised of the two Co-PIs ([name] and [name]) and the trainer from Futures Without Violence ([name]). The internal review board meets by conference call once monthly and can confer on an as needed basis should adverse or difficult events occur. The functions of this internal DSM board are to:Systematically review assessment materials to ensure that assessment was conducted appropriately and that participants disclosing abuse or violence receive appropriate connection to violence-related services and that mandated reports are made by clinicians when appropriate.Systematically review notes from research assistants to ensure that participants experiencing distress were connected directly with the on-site health care provider, receiving educational materials, and being referred appropriately; this included ensuring that all research assistants documented asking each participant about emotional distress after completion of the survey.Conduct on-going preliminary data analyses to evaluate the potential impact of the intervention on specified outcomes of interest (knowledge, self-efficacy, behaviors). In the unlikely event that the intervention appeared to decrease the likelihood of help seeking or increases the distress of participants, the study protocol would be reexamined and modified appropriately.Monitor staff performance with regard to protection of privacy, confidentiality, maintenance of secure databases, and study procedures designed to reduce the risk of distress and potential breaches of confidentiality.Ensure that the PI ([name]), or a designated qualified individual, is available by pager in case research staff needed to confer regarding participant symptoms.Review and report any adverse events associated with the study.

The current project involves monitoring activity across 25 clinics, a much larger undertaking than the pilot study, with follow up of clients up to 15 months from baseline. Given the complexity of this project, in addition to the internal monitoring noted above, we instituted an External Data Safety and Monitoring Board. This external monitoring group consisted of the Quality Assurance Director from Adagio Health, the Vice President of Operations from Planned Parenthood Western Pennsylvania, and Director of Health from Futures Without Violence. All three individuals are familiar with the details of the research protocol, but not intimately involved in the day to day implementation. They also have the authority to suspend the project should any challenges or adverse events arise, and to direct changes in clinic policies and research protocol should site-specific problems emerge. For example, should a client experience emotional distress and the research assistant notified designated clinic staff but the staff is not responsive, this would be reported immediately to the Internal DSMB as well as the External DSMB, and changes would be implemented before proceeding with any further data collection.

### Patient accrual and study flow

25 clinics were combined into 17 clinic clusters for randomization, 8 intervention and 9 control clusters (Fig. 5). From intervention sites a total of 3958 women were approached, 2140 who were excluded either because they didn’t meet inclusion criteria or because they declined to participate, and from control clinics a total of 4259 were approached with 2390 being excluded leaving 3687 who were enrolled into the study and completed the baseline survey (Table 2).

**Fig. 5 Fig5:**
[figure not shown]
CONSORT flow diagram

**Table 2 Tab2:** Demographics of total collected sample (*n* = 3687)

Characteristic	Total %^a^ (n)
Age	
16–20	37.7 (1387)
21–24	35.6 (1310)
25–29	26.8 (986)
Race	
White	80.1 (2951)
Black/African American	13.4 (492)
Hispanic/Latina	1.6 (59)
Multi-racial	3.0 (110)
Other	1.6 (59)
Education	
Less than 12^th^ grade	19.2 (707)
Finished high school	27.0 (995)
Some college	32.9 (1211)
Finished college or grad school	20.3 (748)
US Born	
Yes	98.2 (3615)
No	1.8 (65)
Relationship Status	
Single	32.1 (1181)
Dating more than one person	1.5 (56)
Dating one person/in a serious relationship	58.3 (2148)
Married	7.0 (259)
Married with more sex partners than husband	0.2 (7)
Ever had sexual intercourse	
Yes	97.9 (3604)
No	1.9 (69)
Sex of Sexual Partners^b^	
Men only	88.6 (3184)
Mostly men	7.8 (279)
Equally men and women	1.6 (58)
Mostly women	0.3 (12)
Women only	1.7 (62)

^a^%s may not equal 100 % due to small amounts of missing data

^b^Of those who report ever having had sexual intercourse

### Planned analytic approach

#### Overview

Following a sequence of preliminary analyses to characterize the sample participants and outcome measures, statistical methods for cluster-randomized experimental studies will be used to assess study hypotheses. The anticipated study data is multilevel, with baseline and follow-up data collected from patients, the units of analysis, who are nested within clinics, the units of randomization. The primary assessment of intervention effects will be based on intent-to-treat estimates. As-treated effect parameters will be estimated in secondary analyses and reported as exploratory. Following preliminary phases of descriptive, bivariate and multivariate analyses to characterize the sample and to refine and characterize scale-based outcome measures, estimates and hypothesis testing will be conducted in a multilevel generalized linear mixed (regression) modeling framework that will specify within-clinic and within-patient cluster effects. Regression models will include a parsimonious set of covariates to adjust for the restricted stratified randomization of clinics, to reduce the potential for confounding arising from between-arm imbalances in patient and clinic characteristics, and to increase the precision of intervention effects, with the specification of link and variance functions tailored to the type of outcome variable (e.g., logistic links for binary outcomes).

Two types of biases will be specifically explored using statistical testing. Participation bias will be assessed by comparison of age, race/ethnicity, and other demographics of clients participating in the study with that of the demographics of the overall family planning clinic clients (at participating sites) during the period of data collection, with significant differences noted as potential threats to generalizability. Descriptive statistics and bivariate and multivariate analyses will characterize patient demographics and compare groups with respect to key baseline measures. Variables differing across treatment groups at the p < .20 level will be included as covariates in subsequent adjusted outcome analyses. A similar set of analyses will be conducted to compare those who complete all three visits to those who do not to assess attrition bias. If between-arm differences in attrition are found, this potential validity threat will be noted.

#### Outcome analyses

We will use generalized linear mixed effects models for evaluating the effect of the intervention on follow-up outcomes. Separate models will be created for each outcome, and predictors will include a parsimonious set of important covariates, including potential confounders identified in preliminary analyses, the baseline measure of the outcome (when available), and a clinic-level binary indicator for whether the patient was in a treatment (vs. control) clinic. Random effects will be specified to account for the nesting of patients within clinic and, where appropriate, for repeated follow-up measurements. Recognition of sexual coercion, reproductive coercion, and physical and sexual partner violence baseline measures will be available for all time points and thus baseline measures will be included as covariates in the respective models to improve the precision of our estimated intervention effects. Within-clinic and within-patient cluster effects will be specified as random effects in the models.

For Aim 2 hypotheses, the analysis will be restricted to the patients who report at baseline having recently experienced physical or sexual partner violence or reproductive coercion.

Following the definitive assessments of key study hypotheses, a series of exploratory analyses will be conducted. In particular, the potential for differential impact of the intervention based on patient characteristics will be evaluated, with a view toward identifying factors (e.g., race/ethnicity, age, immigrant status, involvement in commercial sex) that may facilitate or impede the efficacy of the intervention, and to identify patient subgroups most receptive to the intervention or that may require further assistance.

For each outcome, we will use all eligible records at both follow-up visits to model timepoint-specific intervention effects, with the first model specifying (TIMEPOINT x INTERVENTION) interaction terms to permit testing for homogeneity, using Wald-tests with a statistical significance threshold of 0.05. For outcomes without statistically significantly heterogeneous intervention effects, the primary assessment of the intervention will involve the overall main effect of the intervention (versus the control), pooled across both follow-up occasions. Otherwise, timepoint specific contrasts will be used for the primary assessment of the intervention on the outcome. Each outcome will be assessed with a two-tailed alpha = 0.05. No adjustments for multiple testing will be made, as we feel that each of these hypotheses is of independent scientific interest. Graphical and analytical methods will be used to examine model fit and to evaluate assumptions used to justify inferences.

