The ARCHES (Addressing Reproductive Coercion in Health Settings) intervention was developed collaboratively by researchers, advocates and community-based practitioners, with significant input from FP clients [26]. Providers are trained to conduct the three components of the ARCHES intervention: 1) universal client education and assessment regarding IPV and RC; 2) discussion of harm reduction behaviors to reduce risk for unintended pregnancy, IPV victimization, and RC; 3) supported referrals to IPV victim services (including provision of IPV related resources to all clients regardless of disclosure). ARCHES is designed to be implemented within routine FP care, maximizing its feasibility, sustainability and scalability. In the initial pilot randomized intervention trial, among women who at baseline reported experiencing IPV in the past 3-months, the original version of ARCHES reduced the odds of recent pregnancy coercion (a component of RC) at follow-up assessment (3 to 6 months post-baseline) by 71 % compared to the control, highlighting the potential impact of this intervention [26]. Based on this pilot, we designed a large-scale cluster randomized controlled clinical trial (RCT) (i.e., sufficiently powered and of adequate duration) to assess the short (3–4 month) and long-term (12 month) effects of this innovative program on IPV and RC (primary outcomes) as well as unintended pregnancy (secondary outcome) -- major and prevalent health threats among medically underserved women.

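### A 0.05 interaction test chooses the primary contrast for each repeated outcome, so the stated alpha of 0.05 per outcome is not held and the primary contrast depends on the data

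*Protocol article*

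**What the plan says.** The Outcome analyses section fits, for each outcome, a model with "interaction terms to permit testing for homogeneity, using Wald-tests with a statistical significance threshold of 0.05". Two branches follow.

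- Interaction not significant: "For outcomes without statistically significantly heterogeneous intervention effects, the primary assessment of the intervention will involve the overall main effect", pooled over the two follow-up occasions.
- Interaction significant: "Otherwise, timepoint specific contrasts will be used for the primary assessment of the intervention on the outcome".

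The same paragraph states "Each outcome will be assessed with a two-tailed alpha = 0.05" and "No adjustments for multiple testing will be made, as we feel that each of these hypotheses is of independent scientific interest". It gives no rule for turning a T2 result and a T3 result into one conclusion, and no division of alpha between them.

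The Background describes the trial as assessing short-term and 12-month "effects of this innovative program on IPV and RC (primary outcomes) as well as unintended pregnancy (secondary outcome"). Table 1 shows both primary outcomes collected at T2 and T3, so the rule governs both. It also governs the secondary outcomes collected at both follow-ups. It does not affect unintended pregnancy or disclosure, whose follow-up assessment in Table 1 is at T3 only.

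Under Power calculations and sample size, the effective sample sizes for RC and IPV (at least 1000 in Aim 1, at least 424 in Aim 2) assume that T2 and T3 are analysed jointly.

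**The concern.** The contrast that carries the primary conclusion is selected with the same data that then test it. In one branch the outcome gets two tests at the full 0.05. When there is no effect at all, a false-positive interaction means that the T2 and T3 estimates have drifted apart by chance, and this raises the chance that one of them is far from zero. A per-outcome level of 0.05 cannot then be assumed for the whole procedure and has to be checked.

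The question answered is also left open. Depending on the data, the primary result for RC may be a pooled effect while that for IPV is a pair of timepoint effects, or the reverse. Power is given for only one of these possibilities.

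**Working it through.** **1. The plan's own power figures.** Two-proportion test, two-sided 0.05, equal arms, effective n per arm:

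power = Φ{ [|p1 − p2| − 1.96·√(2p̄(1 − p̄)/n)] / √[(p1(1 − p1) + p2(1 − p2))/n] }

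- RC, Aim 1: 10% against 5.3%, n = 500 per arm (1000 in total). (0.047 − 1.96 × 0.01681)/0.01675 = 0.839, so power is 79.9%.
- RC, Aim 2: 26% against 14.9%, n = 212 per arm (424 in total). (0.111 − 1.96 × 0.03918)/0.03880 = 0.882, so power is 81.1%.

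The stated 80% reproduces, but for the pooled contrast only.

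**2. Type I error of the written rule.** Suppose there is no effect at T2 or T3. Let Z2 and Z3 be the two Wald statistics, with correlation ρ and (for the formula) equal variances. Put S = (Z2 + Z3)/√(2(1 + ρ)) and D = (Z2 − Z3)/√(2(1 − ρ)). S is the pooled test and D the interaction test; they are independent standard normal. With s = √((1 + ρ)/2) and d = √((1 − ρ)/2), the larger of |Z2| and |Z3| equals s|S| + d|D|. If either timepoint counts as success:

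α = 0.95 × 0.05 + P(|D| > 1.96 and s|S| + d|D| > 1.96)

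The first term is 0.0475. Because S and D are independent, the pooled test still rejects at 5% among trials that reach it. The second term, by numerical integration and confirmed by simulation with 4,000,000 draws:

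| ρ | timepoint branch | total α, either timepoint | total α, T3 only |
|---|---|---|---|
| 0 | 0.032 | 0.080 | 0.064 |
| 0.25 | 0.026 | 0.073 | 0.060 |
| 0.50 | 0.019 | 0.066 | 0.057 |
| 0.70 | 0.013 | 0.060 | 0.054 |
| 0.90 | 0.007 | 0.055 | 0.051 |

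**3. Which ρ the protocol's inputs imply.** The protocol does not state ρ. Its inputs are 3600 women in 17 clusters, 80% retained at T2 (2880) and 75% of those at T3 (2160), and "residual within-person and within-clinic correlations would be no higher than" 25% and 1%. With m2 and m3 women per cluster and total variance 1, and the clinic effect fully shared between T2 and T3:

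- variance of a cluster mean at T2: 0.01 + 0.99/m2
- variance at T3: 0.01 + 0.99/m3
- covariance: 0.01 + (0.25 − 0.01)/m2

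*Aim 1.* m2 = 2880/17 = 169.4 and m3 = 2160/17 = 127.1. The variances are 0.01584 and 0.01779, the covariance 0.01142, and ρ = 0.01142/√(0.01584 × 0.01779) = 0.68. With these unequal variances and the efficient pooled estimate, α = 0.061 (0.060 with t on 15 degrees of freedom). Given a false-positive interaction, at least one timepoint is significant in 27% of cases. If the clinic effect is only half shared over time, ρ = 0.38 and α = 0.069; if not shared, ρ = 0.09 and α = 0.078.

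*Aim 2.* Take 17% of women as the subset. The protocol gives that figure for recent IPV at baseline, whereas Aim 2 also admits women with RC, so this is an assumption. m2 = 0.17 × 169.4 = 28.8 and m3 = 0.17 × 127.1 = 21.6. The variances are 0.04438 and 0.05583, the covariance 0.01833, and ρ = 0.01833/√(0.04438 × 0.05583) = 0.37. Then α = 0.070. A larger subset would move this towards the Aim 1 figure.

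**4. After a change.** One contrast fixed in advance gives 0.050. Fixed T2 and T3 contrasts at 0.025 each give 0.036 to 0.049 for ρ from 0.9 to 0. Keeping the gate and using 0.025 only inside the timepoint branch still gives 0.052 to 0.069.

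**The case against.** The rule is written down in advance and is mechanical, so no one has discretion over the branch. Timepoint contrasts answer an aim that the Background states, to assess short-term and 12-month effects. The absence of multiplicity adjustment is disclosed. The excess is about one percentage point for Aim 1, and about 95% of null trials go down the pooled branch, where the level is intact. The excess also depends on how the two timepoint results are read. Counting T3 only brings it to 5.1% to 6.4%, and requiring both timepoints removes it. A combining rule could sit in an analysis plan that is not shown.

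Most of this stands as a limit on size. It does not remove the point. Pre-specifying a data-driven choice does not give it the level claimed for it. The reason offered for not adjusting concerns separate hypotheses, not the choice of contrast, or two chances, within one outcome. The gate is in the text, and the text states neither a T3-only nor a both-timepoints rule.

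Three stronger readings are tempting and are not supported. A reader might infer that the plan's confidence intervals are wrong, but this section states none, and pooled inference is essentially unaffected by the selection. A reader might infer that a pooled result would be presented as the 12-month effect, but the text plainly labels it as pooled over both occasions. A reader might infer that after a false-positive interaction one timepoint will usually be significant. On the Aim 1 inputs that happens in 27% of cases.

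**Conclusion.** The point holds in a limited form. As written, the procedure does not hold the stated two-tailed 0.05 per outcome if significance at either timepoint counts as success: about 6.1% for Aim 1 (ρ = 0.68), about 7.0% for Aim 2 (ρ about 0.37), and 5.5% to 8.0% for ρ from 0.9 to 0.

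These figures rest on the either-timepoint reading, on approximately normal Wald statistics, and on the protocol's correlations, which it gives as upper limits. The 6.1% and 7.0% also assume a clinic effect fully shared over time, and the 7.0% assumes a 17% subset with the same retention and correlations as the full sample.

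Apart from the error rate, which contrast is primary depends on the data, and the stated power for RC and IPV applies to only one of the possible answers. This should be corrected. It is a moderate flaw and does not undermine the trial.

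**What to change.** Name the primary contrast in advance for each outcome measured at both follow-ups: the pooled T2 and T3 intervention effect, which is the one that was powered, whatever the interaction test shows. In every case report the T2 and T3 effects with confidence intervals as secondary, and the interaction test as descriptive. This restores 5% per outcome.

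The cost is about one paragraph of analysis-plan wording and the loss of the option to promote a timepoint contrast to primary. The real downside is that a pooled primary effect can average away short- and long-term effects that differ; the timepoint estimates, always reported, would show this.

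An alternative closer to the two stated time horizons is fixed co-primary T2 and T3 contrasts at 0.025 each. That also keeps the error at or below 0.05, but power for RC and IPV would have to be restated. Splitting alpha only within the timepoint branch while keeping the gate is not enough.
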